### ***a. Adherence***

Adherence will be assessed by counting the number of sachets of supplement remaining at the final visit and dividing this into the total number of sachets issued to the participant. This will create a new data point X for all participants. An adherence variable will be created with the formula  $100-X$ . In addition, a categorical variable will be created of low (<50%), medium (51-75%) and high (>75%) adherence.

While the planned intervention period is 12 weeks, this will vary by a number of days for each participant. In order to account for this variation, the number of days between the first and second visit will be calculated. Appropriate adjustments will be made for any participants who have additional days in their intervention period.

### ***b. Figure 3: Analysis Populations***

[figure not shown]

### ***c. Subgroups***

Several subgroups will be formed based on the following characteristics:

1. Sex
2. Age
3. Zygoty
4. Protein intake at baseline
5. Exercise level (IPAQ MET minutes) at baseline
6. Frailty index at baseline
7. SPPB at baseline
8. Gut microbiome alpha diversity at baseline
9. Gut microbiome beta diversity at baseline
10. Gut microbiome responders, defined as those who had changes in the function and/or composition of their gut microbiota from baseline to study end

The primary outcome and relevant secondary outcomes will be re-assessed in these subgroups. It is recognised that the study is not powered for these analyses. Linear mixed models as described in 7.2.1 and 7.2.2 will be carried out in each subgroup. Finally, some subgroups will also be used for group-wide analyses [See Section 5.4], namely protein intake at baseline, and frailty index at baseline.

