## 6. Hypothesis Testing

### *a. Primary Outcome*

The primary aim of the study is to test whether modulation of the gut microbiome using a prebiotic food supplement, in addition to protein supplementation, can improve muscle strength versus protein supplementation alone. Thus, the primary efficacy outcome is a variable which measures muscle strength: chair rise time, the time it takes to rise from a standard chair five times, without using one's arms. This was chosen based on the EWGSOP2 guidance for measuring muscle strength in the context of sarcopenia research.

**Primary outcome:** change in chair rise time, operationalised by using chair rise time measured at end of study, and including baseline chair rise time in the statistical model

**Null Hypothesis:** there is no difference in the change in chair rise time between study arm 1 (prebiotic + protein) and study arm 2 (placebo + protein)

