### **i. Primary Outcome**

The primary analysis will compare intervention groups (arm 1 vs arm 2; blinded) on their change in chair rise time at 12 weeks using a linear mixed model. Chair rise time at 12 weeks will be the dependent variable. Twin clustering will be considered as random effects, treatment group as fixed effect. Baseline value of chair rise time will be included as a covariate [See: ]. If, despite randomisation, there is a difference between the two arms for a specific baseline characteristic, for example age, then age will be included as a covariate in the linear mixed models. The estimated difference in mean change from baseline to 12 weeks and the corresponding 95 % confidence interval (CI) will be presented.

The nature of the design of this study, with randomisation by twin pair and therefore clustering within the data will be taken into consideration by using both twin pair identifier (fid) and zygosity as random effects.

The number of participants who experience a 20% reduction in their chair rise time, as has been deemed clinically significant in previous studies (See Section 3.3), will be presented. We acknowledge that none of these studies used an intervention targeting the gut microbiota, however none such studies were available, making these the closest benchmark available.

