## **1. Gut Microbiome Function and Composition**

Stool samples will be collected from all participants at the beginning and end of the study, via post. The DNA extraction will be carried out in our own laboratory, and then the extracted DNA samples will be sent to an external microbiome sequencing and bioinformatic company, who will carry out high-resolution shotgun metagenomics microbiome analysis of all samples. This includes full profiling of microbiota present (composition), functional species group association analysis, as well as measures of alpha and beta diversity for each individual sample.

Once the above information is available, statistical analysis will assess microbiota differences between the two study arms and between twin pairs. Microbiome composition will be analysed with respect to (1) species diversity, (2) compositional differences, (3) functional differences and (4) differences in abundance of taxa. All analysis will take a hierarchical approach; crude models assessing just the variable of interest (prebiotic supplementation), and models adjusted for key biological (age, sex, exercise etc.) and technical covariates (e.g., differences in library size) will be applied.

Differences in species diversity and richness will be compared between each study arm in regression analysis in crude and adjusted models. Distance matrixes characterise the inter-individual differences in microbiota composition; ordination analyses and permutational multivariate analysis of variance (PERMANOVA) will be used to understand differences in composition between each study arm.

ASVs will be collapsed to family, order, and phylum levels, with hierarchical models, adjusted for each potential mediator individually, then fully adjusted. All models will be adjusted for multiple testing.

All twins within each study arm will be used in paired and unpaired tests to assess if microbiota dissimilarity increased with differences in muscle strength, taking relevant covariates (including diet [HEI], BMI and frailty index) into consideration.

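### The SAP compares the arms within gut microbiome responders, a group formed after randomisation by a change the prebiotic is meant to cause, and no subgroup analysis tests an arm-by-subgroup interaction

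*Combined protocol and SAP*

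**What the plan says.** SAP section 5.3 (Subgroups) names ten characteristics. Items 1 to 9 are sex, age, zygosity and six baseline measurements. Item 10 is "Gut microbiome responders, defined as those who had changes in the function and/or composition of their gut microbiota from baseline to study end". No threshold or direction of change is given, and people in either arm can qualify.

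The use of these groups is stated in three sentences: "The primary outcome and relevant secondary outcomes will be re-assessed in these subgroups"; "It is recognised that the study is not powered for these analyses"; and "Linear mixed models as described in 7.2.1 and 7.2.2 will be carried out in each subgroup". Section 7.2.1 is the arm contrast: "The primary analysis will compare intervention groups (arm 1 vs arm 2; blinded) on their change in chair rise time at 12 weeks". The primary aim in section 6.1 is to "test whether modulation of the gut microbiome using a prebiotic food supplement, in addition to protein supplementation, can improve muscle strength", so the variable that defines item 10 is one the treatment is intended to move.

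The SAP gives no interaction test, no cut-points or number of levels, and no multiplicity rule for subgroups. Its multiplicity statements cover serum metabolites (7.2.2) and the microbiome models (7.2.2.1). Section 7.1 sets the significance threshold at 0.05, and subgroup results are a planned table (Table 9 in section 7.6).

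**The concern.** Randomisation makes the arms comparable in everything that precedes treatment. It does not make them comparable within a group selected on something that treatment changes. If the prebiotic makes some people responders who would not otherwise have been, the prebiotic responders include them and the placebo responders do not. Anything that drives both microbiome change and chair-rise change then differs between the two sets. Background diet, activity and intercurrent illness are plausible examples: participants keep their normal diet, and both arms are encouraged to exercise. The contrast can then be non-zero when the prebiotic has no effect on chair-rise time.

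This matters because the trial asks whether the microbiome modulates anabolic resistance, and an arm difference confined to responders looks like an answer.

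The second issue is separate. A within-stratum arm contrast tests whether there is an effect in that stratum. It does not test whether the effect differs between strata, which is the purpose of a subgroup analysis. With many such tests and no multiplicity rule, a chance finding in one stratum has nothing to hold it in check.

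**Working it through.** Section 5.3 states no figure of its own to reproduce. The only yardstick is the planned effect in section 3.3: |log10(0.8)| / 0.126 = 0.0969 / 0.126 = 0.77 SD.

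**1. Responder contrast under a true null.** All inputs here are assumptions, because the documents give none.
- Microbiome change score: M = s × T + e, with T = 1 for prebiotic, e standard normal and s the treatment shift in SD (0, 0.5 or 1.0).
- Outcome in SD units: no treatment effect, correlation ρ with e (0.3 or 0.5) through a shared cause.
- Bias = ρ × (mean of e in prebiotic responders − mean of e in placebo responders).

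*Rule A, directional change above the pooled median (cut-off s/2).* The difference in means is φ(s/2)/Φ(s/2) − φ(s/2)/[1 − Φ(s/2)].
- s = 0.5: 0.646 − 0.964 = −0.318; bias −0.095 (ρ = 0.3) or −0.16 (ρ = 0.5).
- s = 1.0: 0.509 − 1.141 = −0.632; bias −0.19 or −0.32.
- s = 0 or ρ = 0: bias 0.

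*Rule B, change in either direction, |M| above its pooled median c.* Placebo responders have mean e of 0 by symmetry. Prebiotic responders have mean [φ(c − s) − φ(c + s)] / [1 − Φ(c − s) + Φ(−c − s)].
- s = 0.5, c = 0.716: 0.379; bias +0.11 or +0.19.
- s = 1.0, c = 0.837: 0.535; bias +0.16 or +0.27.

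*Loose rule, 90% of participants classed as responders.* Directional: −0.04 to −0.12. Undirected: +0.02 to +0.04.

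The range is therefore about −0.3 to +0.3 SD. The sign depends on the responder rule, and it reverses again if ρ is negative. Rule A's largest value is 0.32/0.77 = 41% of the planned effect and its smallest is 0.095/0.77 = 12%.

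**2. Check in the trial's own structure.** A null simulation of 36 twin pairs, one twin per arm, used a baseline-adjusted random-intercept model and assumed responder rates in placebo/prebiotic.
- 30%/30%, or no shared cause: bias about 0.
- 30%/60% with a shared cause: +1.3% to +3.9% of chair-rise time.
- 20%/80% with a shared cause: +3.1% to +8.0%, with 12–18% rejection against about 5% in the full sample.

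Rejection was already 9–12% in responder subgroups with no bias, because few intact pairs remain. Only part of the 12–18% comes from conditioning on response.

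**3. Number of tests.** Assume two levels for each of ten factors, primary outcome only: 10 × 2 = 20 tests.
- Expected false positives: 20 × 0.05 = 1.0.
- Chance of at least one if independent: 1 − 0.95^20 = 64%.
- Nine baseline factors alone: 18 tests, 1 − 0.95^18 = 60%. Simulated with overlapping strata in 36 pairs, it was 54%.

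**The case against.** The strongest reply is that little depends on this. The primary analysis is intention-to-treat on all randomised participants and does not use the subgroups. Section 5.3 already admits low power. The responder rule is so loose that, read literally, almost everyone could qualify, and the group would then be close to the full sample; with 90% responders the illustrative bias falls to at most about 0.12 SD. The shift and correlation come from outside the documents. All of this stands, and it limits the weight of the point. It does not repair it: a warning about power concerns missed effects, not bias or false positives, and an undefined threshold leaves the rule open.

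A reader might also infer three stronger things that the documents do not support.
- *Many false positives.* Ten factors, two levels and seven outcomes would give 140 tests and 7 expected. The SAP fixes neither the number of levels nor which secondary outcomes are relevant, so this is a constructed upper scenario.
- *Bias from split twin pairs.* Age and zygosity do not split pairs, and sex does not split same-sex pairs. Where other baseline factors do, a single twin can stay in the random-effects model and the comparison remains randomised. The cost is precision only.
- *The same fault in the microbiome models* that section 7.2.2.1 says will be "adjusted for each potential mediator individually, then fully adjusted". That section does not name the mediators or say that they are measured after baseline, and crude models are run as well.

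**Conclusion.** The point holds for item 10 and for the missing interaction test. The planned arm contrast among responders is not a randomised comparison, and no other section of the protocol or SAP turns it into one. Bias requires two conditions: that the prebiotic changes who responds, which is its purpose, and that microbiome change and chair-rise change share a cause, which is plausible but not documented. If either fails, the bias is zero. The interval of about −0.3 to +0.3 SD is illustrative and should not be quoted as an estimate.

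For the nine baseline factors the contrasts are unbiased, but the plan never tests whether the effect differs between levels. The 64% figure rests on assumed two-level factors and independent tests; the expected count of about 1 needs only the number of levels and valid 5% tests.

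This should be fixed. It does not threaten the primary result.

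**What to change.** - **Item 10.** Remove it from the arm-comparison subgroups. Report microbiome change against chair-rise change as an association, labelled observational and exploratory.
- **Baseline factors.** For each, fit one mixed model on all randomised participants with an arm × baseline-characteristic interaction, keeping the characteristic continuous where it was measured so. Report the interaction estimate with its 95% CI and label the results exploratory. This keeps every pair in the model. It also avoids fitting the section 7.2.1 model, which is specified as "using both twin pair identifier (fid) and zygosity as random effects", inside a stratum that has only one zygosity.
- **Item 9.** Beta diversity is a distance between samples. State a per-person baseline summary or omit the item.

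The cost is SAP wording and code. Stratum-specific p-values give way to interaction estimates with low power. Take the planned effect present in one half only, 15 to 18 per arm in each half, and ignore the pairing: the standard error is 0.126 × √(4/15) = 0.065 to 0.126 × √(4/18) = 0.059, and power is 32% to 37%. A stratum model on the same half has 53% to 61% power for the effect in that half, but it answers a different question. Nine interaction tests on the primary outcome would carry a 1 − 0.95^9 = 37% chance of at least one false positive if independent and unadjusted (4.9% with Bonferroni at 0.05/9), which is why the exploratory label is needed.

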### ***d. Overall Improvement***

In addition to analysing the primary and secondary outcomes by arm, group-wide comparisons will be carried out for the following variables of interest: weight, BMI, SPPB

score, balance score, grip strength, chair rise time, gait speed, IPAQ MET minutes/week, IPAQ score, SNAQ score, CANTAB cognitive test results and serum metabolites.

Paired tests will be carried out to assess for differences between baseline and study end point, two sample t-tests for continuous variables (normally distributed), Mann-Whitney test for non-normally distributed continuous variables, and Pearson's chi-squared tests for categorical variables.

While there is no control group for these analyses, these will tell us whether the protein and exercise intervention that all twins will receive was beneficial for the aforementioned variables of interest, irrespective of gut microbiome modulation with a prebiotic food supplement. This analysis will also be repeated using two subgroups of interest, protein intake at baseline, and frailty index at baseline.

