| Vitamin B12 µg/d             | 3.5 (1.9)      | 4.4 (2.3)      | 3.7 (2.0)      |  | 2.9 (1.6)      | 2.6 (1.3)      | 0.026* |
| Folate µg/d                  | 222.1 (82.9)   | 212.5 (77.3)   | 220.0 (81.2)   |  | 183.8 (77.1)   | 212.8 (99.9)   | 0.079  |
| Vitamin C µg/d               | 91.4 (73.9)    | 61.9 (26.1)    | 84.9 (67.3)    |  | 69.9 (47.3)    | 72.4 (43.5)    | 0.084  |
| Vitamin D µg/d               | 3.5 (3.8)      | 2.9 (1.9)      | 3.3 (3.4)      |  | 2.7 (2.3)      | 2.1 (2.8)      | 0.200  |
| 25-Hydroxy D3 µg/d           | 0.0 (0.1)      | 0.0 (0.0)      | 0.0 (0.1)      |  | 0.4 (1.2)      | 0.0 (0.2)      | 0.092  |
| Vitamin D3 µg/d              | 0.3 (0.6)      | 0.6 (0.9)      | 0.4 (0.7)      |  | 0.3 (0.7)      | 0.3 (0.8)      | 0.228  |
| Vitamin E µg/d               | 8.0 (3.3)      | 8.9 (5.8)      | 8.2 (3.9)      |  | 6.2 (2.6)      | 8.2 (5.1)      | 0.014* |
| Vitamin K1 µg/d              | 78.3 (89.5)    | 54.7 (37.4)    | 73.1 (81.3)    |  | 50.2 (37.8)    | 49.1 (53.5)    | 0.442  |
| Food groups and other |                |                |                |  |                |                |        |
| Vegetables g/d               | 160 (120)      | 107 (63)       | 149 (112)      |  | 141 (64)       | 95 (61)        | 0.469  |
| Fruits g/d                   | 143.5 (104.2)  | 148.9 (107.7)  | 144.7 (104.0)  |  | 141.2 (141.5)  | 143.1 (92.2)   | 0.167  |
| Alcohol g/d                  | 9.7 (15.6)     | 18.6 (21.3)    | 11.6 (17.2)    |  | 7.7 (8.7)      | 13.5 (19.8)    | 0.063  |
| Water g/d                    | 1931.3 (625.8) | 2075.4 (840.2) | 1963.0 (673.4) |  | 1858.9 (622.3) | 1848.2 (782.2) | 0.124  |
| Missing Data (n)             | 10             | 3              | 13             |  | 20             | 4              | 24     |

All data presented as mean (standard deviation). Please note the nutritional intake from the intervention sachet is not included in these dietary data. NSP: non-starch polysaccharides. AOAC fibre comprises of the total amount of non-digestible polysaccharides, and includes e.g., lignin and resistant starches, measured with a set of methods developed by the Association of Analytical Chemists (AOAC). \* Denotes significance.

P values are within group comparisons of the total population between baseline and end of intervention performed using a two-sided paired t-test

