|--------------------------------------|------------------------------------------------------------------------------------------------------------------------------------------------------------------------------------------------------------------------------------------------------------------------------------------------------------------------------------------------------------------------------------------------------------------------------------------------------------------------------------------------------------------------------------------------------------------------------------------------------------------------------------------------------------------------------------------------------------------------------------------------------------------------------------------------------------------------------|
| Number of Subjects/Patients          | The sample size has been calculated to detect effect in chair-rise time; 70 individuals will have 80% power at 0.05 alpha to identify a difference of 3.5 seconds (effect size in 35 people per group, over 12 weeks) (20% dropout rate).                                                                                                                                                                                                                                                                                                                                                                                                                                                                                                                                                                                    |

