### **3. Study Methods**

#### ***Trial Design***

The trial design is described in detail in previously published study protocol ([name] et al., 2021) and briefly described here.

The study is a randomised, placebo controlled, double blinded, intervention study in which participants were grouped into two different arms. One arm received protein food supplement plus prebiotic food supplement and the other arm received protein food supplement plus placebo (maltodextrin). Supplements were posted to participants in pre-mixed identical sachets, which they were advised to take daily for 12 weeks, in a glass of water or other drink. Participants in both groups were also advised to undertake resistance exercises. All participants had a study visit carried out via video teleconferencing software at the beginning and end of the study. They also completed questionnaires, food diaries and cognitive testing remotely at the beginning and end of the study. Lastly the participants also collected biological samples (urine, stool, saliva, and capillary blood) and posted these to the department at the beginning and end of the study. A subset of participants also completed an additional study visit in-person at the department for validation measures.

Randomisation was used to control for equal distribution of key characteristics that may confound between group comparisons. Participants were randomised as twin pairs, with one twin from the pair in the prebiotic food supplement arm and one twin from the pair in the placebo arm. Twin pairs are matched for age and often for sex, early environment, baseline genetic sequence, socioeconomic status etc., proving a strong model for detecting changes while adjusting for both observed and unobserved confounding.

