## **7. Statistical Analysis**

### ***a. Descriptive Statistics***

All outcomes will be presented using descriptive statistics; normally distributed data by the mean and standard deviation (SD) and skewed distributions by the median and interquartile range (IQR). Binary and categorical variables will be presented using counts and percentages. P values of  $\leq 0.05$  will be considered sufficient to reject the null hypothesis.

Outliers will be assessed by examining plots and checked for possible erroneous entry. Where necessary, results with and without outliers will be compared to assess for discrepancies in the results, and this will be discussed if found to be discrepant.

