#### ***i. Food diary data***

The food diary data will be presented in tables, by sex. Paired tests will be carried out to assess for differences between baseline and study end point, two sample t-tests for continuous variables (normally distributed), and Mann-Whitney test for non-normally distributed continuous variables.

Over and under reporting will be assessed using the Goldberg energy intake to BMR (basal metabolic rate) ratio method . BMR will be calculated using the revised Harris-Benedict equation , and multiplied by an adjustment factor for physical activity . A ratio of this adjusted BMR to energy intake (kcal/day) will be generated. Over and under reporters will be identified as those who are two standard deviations above or below this ratio. If over an/or under reporters are identified, an additional dietary table will be presented, with these participants excluded.

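### The group-wide before-after tests have no twin-pair term and do not settle which test is meant; if paired within person, a nominal 5% test would reject in about 6–11% of cases for an assumed within-pair correlation of change of 0.1–0.5

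*Combined protocol and SAP*

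**What the plan says.** The SAP's Trial Design section allocates each pair "with one twin from the pair in the prebiotic food supplement arm and one twin from the pair in the placebo arm". Any analysis that pools the arms therefore contains both members of a pair. The supplement reports 72 participants (Table S1), 36 per arm (Table S6), which makes 36 pairs.

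SAP 5.4 states that "group-wide comparisons will be carried out for the following variables of interest" and lists about a dozen: weight, BMI, the physical performance measures, activity, appetite, CANTAB results and serum metabolites. The method is "Paired tests will be carried out to assess for differences between baseline and study end point, two sample t-tests for continuous variables", with Mann-Whitney for skewed variables and Pearson's chi-squared for categorical ones. The section acknowledges that there is no control group, but says the tests will show whether the protein and exercise given to everyone was beneficial. It repeats them in subgroups by baseline protein intake and frailty index.

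SAP 7.1(i), on the food diaries, uses the same opening, "Paired tests will be carried out to assess for differences between baseline and study end point", and again names two-sample t and Mann-Whitney tests.

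SAP 7.2.1 says that the design, "with randomisation by twin pair and therefore clustering within the data will be taken into consideration", through random effects for twin-pair identifier and zygosity. That method carries over to the secondary arm comparisons (7.2.2) and the subgroup mixed models (5.3). It does not reach 5.4 or 7.1(i). Under SAP 7.1, p values of 0.05 or less "will be considered sufficient to reject the null hypothesis".

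**The concern.** In the arm comparison, positive correlation between co-twins helps, because the contrast is formed within the pair. In a pooled mean change it hurts, because two co-twins' changes carry less information than two unrelated people's. A person-level test ignores this. The plan accounts for the pair where doing so gains precision and omits it where ignoring it can understate the error.

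The before-after p value is the only statistical support offered for saying that the shared programme worked, and it is a planned table (Table 3 in the SAP's list). If its true level exceeds 5%, some claims of improvement will be chance findings presented at a threshold they do not meet.

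The wording adds a second problem. A paired test and a two-sample test of baseline against end are different analyses, and their errors run in different directions here.

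**Working it through.** **Inputs.** From the documents: 36 pairs of two, and a 0.05 threshold (two-sided in the reported tables). Not in the documents, so assumed: the within-pair correlation of 12-week change (ICC), taken as 0.1–0.5, and the within-person correlation r between baseline and end.

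**Reading 1: within-person paired t-test on 72 changes.** With complete pairs, the variance of the mean change is (1 + ICC) times the value the test assumes. The true level is about 2 × [1 − Φ(1.96 / √(1 + ICC))], and the effective sample size is 72 / (1 + ICC). At ICC 0 this returns the plan's nominal 5.0%.

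| ICC of change | True SE ÷ SE used | Level of a nominal 5% test | Effective n |
|---|---|---|---|
| 0 | 1.00 | 5.0% | 72 |
| 0.1 | 1.05 | 6.2% | 65.5 |
| 0.2 | 1.10 | 7.4% | 60 |
| 0.3 | 1.14 | 8.6% | 55.4 |
| 0.5 | 1.22 | 10.9% | 48 |

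Simulation with 36 pairs (40,000 runs per setting) agrees: 7.1–7.2% at ICC 0.2 and 10.9–11.1% at 0.5. The Wilcoxon signed-rank test gives 6.8% and 10.7% (10,000 runs). A t-test on the 36 pair means stays at 4.8–5.1% for every ICC from 0 to 0.7.

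**Incomplete pairs.** With some co-twins single, the factor becomes 1 + ICC × (people in complete pairs ÷ people analysed). Table S3 shows 26 people with end-of-study CANTAB data. If these were 10 pairs and 6 singles (an assumed split), the factor is 1 + 0.2 × 20/26 = 1.154 at ICC 0.2 and 1 + 0.5 × 20/26 = 1.385 at ICC 0.5. The levels are then 6.8% and 9.6%.

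**Reading 2: the two-sample t-test as literally named.** This test ignores the correlation within a person. True variance divided by assumed variance is (1 − r)(1 + ICC), on the simplifying assumption that baseline and end have equal variance and the same within-pair correlation.

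- r = 0.3: 0.7 × 1.2 = 0.84 at ICC 0.2 and 0.7 × 1.5 = 1.05 at ICC 0.5. Simulated levels are 3.2% and 5.8%.
- r = 0.6: 0.48 and 0.60. Simulated levels are 0.6% and 1.1%.
- r = 0.8: 0.24 and 0.30. Simulated levels are below 0.1%.

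The literal test is conservative whenever r exceeds ICC / (1 + ICC), which is 0.17 at ICC 0.2 and 0.33 at ICC 0.5.

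**Which reading was used?** The Table S4 footnote says "P values are within group comparisons of the total population between baseline and end of intervention performed using a two-sided paired t-test". Its summary figures fit that: 72 − 13 = 59 people had baseline diaries and 72 − 24 = 48 had end diaries, and an unpaired test of energy (1569.5, SD 397.7, against 1476.0, SD 438.7) gives p = 0.25, whereas 0.021 is reported. There are also signs that co-twins were treated as independent in a simple comparison. For baseline weight by arm in Table S6, an unpaired test on 71.8 (14.0) and 75.8 (17.2), 36 per arm, gives 0.28, which is the reported value. For BMI it gives 0.25 against 0.24 reported. This evidence is indirect, because neither table is the group-wide table planned in 5.4.

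**The case against.** The strongest reply is that the inflation depends on a correlation nobody has documented. The plan describes co-twins as matched on age, often on sex, and on genes and early environment. That supports similarity in levels, not in 12-week changes, which also carry the measurement error of remotely supervised tests. This stands: a positive ICC of change is plausible but not established, and at zero there is no inflation.

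It also stands that the tests literally named would mostly reject too rarely, so the direction of the error depends on settling the wording. The Table S4 footnote favours the within-person reading. However, near-identical footnotes sit under Tables S3 and S7, whose p values compare groups, so footnote wording alone is weak evidence.

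A reader might infer more than the documents allow:

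- **That every listed outcome is tested too liberally.** This holds only on the paired reading with positive ICC, and by less where pairs are incomplete.
- **That planned confidence intervals are too narrow.** SAP 5.4 plans tests and no intervals. The problem would affect only an interval later built from the same standard error.
- **That the significant diet changes in Table S4 are false.** The number of people paired is not reported. Assuming 40–46 people, all in complete pairs, and dividing t by √(1 + ICC) with n/2 − 1 degrees of freedom, no starred result crosses 0.05 at ICC 0.1. At 0.2 only fat does (0.032 becomes about 0.056). At 0.5 energy, fat and B12 do, while vitamin E stays at about 0.049. The conclusion changes with the assumed ICC.

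Finally, this is a supplementary analysis without a control group. A correct standard error would not turn a before-after change into evidence that the programme caused it.

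**Conclusion.** The point holds conditionally. SAP 5.4 and 7.1(i) pool both co-twins with no pair term, nothing else in the documents supplies one, and the test is described inconsistently.

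For a within-person paired test with 36 complete pairs and an assumed ICC of change of 0.1–0.5, the standard error is understated by a factor of 1.05–1.22, and a nominal 5% test has a true level of about 6–11%. For the literal two-sample test the level is mostly below 5%, often far below. Under neither reading can the stated threshold be relied on unless the correlations happen to be favourable.

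The primary and secondary arm comparisons model the pair and are not touched. The change is worth making because the section sets out to say whether the programme was beneficial, but it does not threaten the trial's main conclusion.

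**What to change.** In SAP 5.4 and 7.1(i), replace the list of tests with one within-person analysis of change that respects the pair. There are two workable options:

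- Fit each person's change (end minus baseline) with an intercept and a random twin-pair effect, keeping a co-twin without a partner's value as a one-member cluster.
- Average the two co-twins' changes and apply a one-sample t-test to the pair values, or a signed-rank test if they are skewed.

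For categorical items, use a within-person test with pair-clustered errors in place of Pearson's chi-squared. Apply the same rule to the two repeated subgroup analyses. If intervals are reported, build them from the pair-respecting standard error, and state how many complete pairs and single co-twins enter each analysis.

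The cost is a sentence or two in each section and a re-run of simple models, with no new data. If tests paired within person would otherwise have been used, p values may become slightly less favourable. If the ICC of change is near zero, little is lost.
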